## Methods/Design

The Glaucoma Initial Treatment Study (GITS) is a multi-centred, cluster randomised, controlled, clinical trial comparing two treatments for patients with POAG and XFG. Treating investigators and patients are not masked to treatment allocation due to the nature of the treatments; however, the QoL questionnaire administrators are masked to treatment allocation.

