#### Baseline characteristics

Analyses will be performed for all variables at baseline to detect potential bias in recruitment. Continuous variables will be reported using means ± standard deviations (SD) or median (interquartile range (IQR)). For dichotomous/categorical variables, absolute numbers and percentages will be computed, together with their 95 % confidence intervals (CI). The comparison of means will be carried out using Student’s t test, the Mann-Whitney test, analysis of variance or the Kruskall-Wallis test as appropriate. The difference in proportions between the two treatment groups will be carried out using Chi-square statistics. These comparisons will be made by assessing the prognostic relevance of the difference observed, not through hypothesis testing. Baseline summaries with respect to the main covariates will be presented and discussed from a clinical point of view, irrespective of whether a statistical test indicated a ‘statistically significant difference’ between treatment groups. If we find a strong baseline imbalance in a variable, we will include this variable as a covariate in a sensitivity analysis to allow assessment of the robustness of the conclusions drawn from the primary analysis.

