#### Primary analysis

The primary analysis will be ITT analysis, which includes all randomised patients in the groups to which they were randomly assigned, regardless of their adherence with the entry criteria, the treatment they actually received, and of subsequent withdrawal from treatment or deviation from the protocol. The ITT analysis will include all patients with 24-month GOAT, Glau-QoL, and AQoL-7D data. The GOAT will be our main primary outcome. The GOAT and Glau-QoL data will initially undergo Rasch Analysis (a form of Item Response Theory - IRT) using Winsteps software (version 3.90), Chicago, Illinois [45].

We will examine the missing data mechanism (probability distribution of missingness) to determine whether it is missing completely at random (MCAR), missing at random (MCR) or missing not at random (NMAR). Since patient-centred measurements will recur on the same patients, longitudinal HRQoL data will be analysed using multivariate generalised estimating equation (GEE) or generalized linear mixed models (GLMMs). We will adjust for pre-defined variables that we consider are associated with the primary outcome (HRQoL) from the literature. These include clinical variables (for example, baseline glaucoma severity, visual field, visual acuity, optic disc changes, duration of glaucoma), and sociodemographic variables (for example, age, gender). Separate regressions will be conducted for each QoL parameter. These models take into account the correlation within observations on the same subject and allow for inclusion of data on subjects who have only partial follow-up without imputing missing data. To handle multiplicity in the multiple regression models, Bonferroni adjustment will be used.

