### Sample size estimation

The sample size for the study is based on the primary outcome measure of HRQoL at 24 months post-treatment. Our hypothesis is that compared with topical medication, SLT treatment will have a significantly greater positive impact on HRQoL. Mean and standard deviations for the pilot data of GOAT and previous work with the Glau-QoL were used [36, 38]. To detect a 0.156 Logit difference (effect size of 0.3) on the Rasch-analysed GOAT and Glau-QoL at 80 % power with a 5 % level of significance, 175 patients will be needed in each group. Similarly, the mean and standard deviation values for the AQoL-7D were obtained from the literature [39, 47]. To detect a 0.7 difference (effect size of 0.3) on the AQoL-7D between the two groups at 24 months with 80 % power at 5 % level of significance; 176 patients will be needed for each group. Assuming an attrition rate of 15 % after 2 years, 193 patients will be enrolled in each group at baseline. Furthermore, for Aim 3, the study will also have 79 % power to detect a 10 % difference in ‘success rate’ of IOP (defined as ≥25 % reduction in baseline IOP) in the SLT group compared with topical medication using a two-sided log-rank test at the 5 % significance level.

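### The plan aims to determine whether missing quality-of-life scores are MCAR, MAR or NMAR, but observed data cannot separate MAR from NMAR, so a MAR verdict would be unfounded assurance

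*Protocol article*

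**What the plan says.** All of this is in the protocol article.

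- **Primary analysis, aim.** The mechanism of missingness will be examined "to determine whether it is missing completely at random (MCAR), missing at random (MCR) or missing not at random (NMAR". The section names no test or other method for doing so, and does not say what follows from any of the three answers.
- **Primary analysis, model.** "longitudinal HRQoL data will be analysed using multivariate generalised estimating equation (GEE) or generalized linear mixed models (GLMMs". The models are said to "allow for inclusion of data on subjects who have only partial follow-up without imputing missing data". The choice between the two is left open.
- **Primary analysis, population.** "The ITT analysis will include all patients with 24-month GOAT, Glau-QoL, and AQoL-7D data".
- **Baseline characteristics.** The one sensitivity analysis the article names for the primary result concerns baseline imbalance: "we will include this variable as a covariate in a sensitivity analysis to allow assessment of the robustness of the conclusions". The sensitivity analyses under Economic analysis belong to the cost-effectiveness evaluation.
- **Sample size estimation.** "Assuming an attrition rate of 15 % after 2 years", with 193 patients enrolled per arm.
- **Methods/Design.** "Treating investigators and patients are not masked to treatment allocation due to the nature of the treatments", but "the QoL questionnaire administrators are masked to treatment allocation".
- **Statistical analysis plan.** Analyses follow a pre-specified analytical plan, which is not shown.

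**The concern.** The three labels describe how the chance of a score being missing relates to the data. Under MCAR it relates to nothing, under MAR only to what was observed, and under NMAR also to the unseen score. Comparing patients who stay with patients who leave, on their earlier scores and covariates, can show that MCAR is false. It cannot show whether, among patients with the same observed history, those who left would have scored worse. A plan to determine which of the three holds therefore promises an answer the data do not contain.

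This matters because the model's validity rests on that answer. A likelihood-based mixed model on available data is valid under MAR if correctly specified. Unweighted GEE generally needs MCAR, or missingness that depends only on covariates in the model. With GEE or GLMM left open, a supposed finding about the mechanism could be used to justify either.

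The setting gives some reason for care. The primary outcome is reported by patients who know their treatment. Masked interviewers limit interviewer bias but do not stop a dissatisfied patient from leaving. Under Topical ocular hypotensive therapy, patients who have crossed over with both regimens leave the trial, so loss can follow treatment response.

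**Working it through.** **1. Why the classification cannot be made.** Let R mark which scores are observed. The joint distribution factors as

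f(observed, missing, R) = f(observed, R) × f(missing | observed, R).

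The data inform only the first factor. The second can be set to what MAR implies, or shifted from it by any amount, and the observed data do not change. No examination of them can choose between the two.

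**2. Numerical demonstration (all settings assumed).** In 400,000 simulated patients, the earlier score is standard normal, the final score is 0.6 × earlier score + 0.8 × independent noise, and the log-odds of being observed are 1.9 + 0.5 × earlier score. This gives 14 % missing. The unseen final scores are then shifted by 0 (MAR), −0.5 or −1 SD (both NMAR).

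| Shift of unseen scores | True mean | Estimate assuming MAR | Completer mean |
|---|---|---|---|
| 0 | −0.001 | −0.0017 | 0.0395 |
| −0.5 SD | −0.071 | −0.0017 | 0.0395 |
| −1 SD | −0.141 | −0.0017 | 0.0395 |

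The last two columns do not move. Only the truth moves, by 0.14 × shift (0.07 and 0.14).

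**3. The plan's own base figure.** The target is 0.156 logit, effect size 0.3, so the implied SD is 0.156 / 0.3 = 0.52 logit. With 80 % power and two-sided 5 %:

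n per arm = 2 × (1.96 + 0.842)² / 0.3² = 174.5, rounded up to 175.

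This reproduces the stated 175. With 193 enrolled and 15 % loss, 193 × 0.85 ≈ 164 per arm have 24-month data. (That 164 is below 175 is a separate matter and is not used here.)

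**4. Size of the possible bias (the shift is an assumption).** If a fraction f of one arm is missing and those scores lie k SD below their MAR prediction, while missing scores in the other arm follow MAR, then

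bias = f × k.

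For the type I error, take the standard error of an unadjusted comparison of 164 per arm, √(2/164) = 0.110 SD. With no true effect, two-sided type I error = 1 − Φ(1.96 − bias/SE) + Φ(−1.96 − bias/SE).

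| k (SD) | Bias at f = 0.15 (SD) | In logits (× 0.52) | Share of 0.3 SD target | Type I error |
|---|---|---|---|---|
| 0.3 | 0.045 | 0.023 | 15 % | 6.9 % |
| 0.5 | 0.075 | 0.039 | 25 % | 10.4 % |
| 1.0 | 0.150 | 0.078 | 50 % | 27.4 % |

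At k = 0.5, the bias is 0.05 SD with 10 % missing and 0.10 SD with 20 % missing. If both arms have the same f and k, the biases cancel. If the poor missing scores are in the drops arm, the bias is against SLT. If they are in the SLT arm, it favours SLT.

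**5. Where a positive result would tip.** The smallest significant difference is 1.96 × 0.110 = 0.216 SD. An observed difference of exactly 0.3 SD would lose significance at a one-arm shift of (0.3 − 0.216) / 0.15 ≈ 0.56 SD.

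**The case against.** Several points on the other side are sound.

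- **No decision rule is stated.** A reader might infer that informative loss will be passed as ignorable. The article does not say so. It lists NMAR among the possible answers, names no test and attaches no action to any verdict. What can be said is that a MAR verdict, if reached, would not be supported by the data.
- **The analytical plan is not shown.** A reader might also infer that the primary result is left untested against departures from MAR. That would be an argument from absence in a condensed article. Missing-data sensitivity analyses are commonly placed in the analytical plan, and the unseen one may contain them.
- **The bias figures do not measure the sentence.** They show what NMAR loss does to any analysis that assumes MAR. Rewording the sentence changes none of them. They indicate why the assurance matters, not how much harm the wording does.
- **The shifts and the arm difference are assumed.** The Discussion attributes possible dropout to the burden of participation, which falls on both arms, and describes training to improve retention. Nothing in the article gives an arm difference or a direction, and a 1.0 SD shift confined to one arm is pessimistic.
- **Masking is partial, not absent.** The quality-of-life interviewers are masked.

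All five limit the consequence. None makes the stated aim achievable: that is a wrong statement on the page, not a detail left to another document.

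**Conclusion.** The point holds in a limited form. The Primary analysis section commits to a classification that observed data cannot provide. MCAR can be contradicted, but MAR and NMAR cannot be separated without untestable assumptions. Any MAR conclusion from this step would be unfounded support for an available-data GEE or mixed-model analysis.

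The core rests on no numerical assumption. The illustrative size, 15 % to 50 % of the target effect and type I error of about 7 % to 27 %, assumes 15 % missing, a shift of 0.3 to 1.0 SD in one arm only, and an unadjusted standard error with 164 per arm. The documents give only the attrition rate and the enrolment. The claim does not extend to saying that informative loss will be ignored or that no sensitivity analysis exists.

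**What to change.** In the Primary analysis section:

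1. Replace the aim of determining the mechanism with a descriptive comparison by arm of dropout rates, reasons for dropout and last observed scores. Correct the MCR misprint if the terms are kept.
2. State that the primary GOAT analysis takes MAR as its working assumption. This favours the likelihood-based mixed model over unweighted GEE, so the open choice should be closed accordingly.
3. Add, or point to in the analytical plan, a delta-adjusted (tipping-point) analysis of the 24-month GOAT difference. Multiply impute under MAR, shift the imputed scores separately in each arm over a pre-stated range (for example 0 to −0.5 SD, widened if needed to reach the tipping point), and report the shift at which the conclusion changes.
4. Make clear how this fits with the sentence limiting the analysis to patients with 24-month data, since the models are meant to use partial follow-up.

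The cost is one paragraph, one further analysis and one table, with no new data. It should be fixed before outcome data by arm are seen. The downside is that the table may show the result to be fragile.

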### Randomisation

Randomisation schedules developed by the Centre for Eye Research Australia (CERA) Melbourne, (Coordinating Centre), using a list of computer generated pseudo-random numbers are designed to yield an assignment ratio of 1:1. Randomisation, per person, will be stratified by clinical centre and type of glaucoma. The randomization number will be assigned to a patient sequentially according to the order of enrolment within the stratum. The treatment assignment form, contained in an opaque envelope will be filed in the patient’s ‘Unmasked study folder’ with the patient’s screening code completed on this form. Sites will then scan a copy of the treatment assignment and email this to the Coordinating Centre for its records. When the number of envelopes on site reaches only four remaining, the site will notify the Coordinating Centre, which will send more envelopes containing treatment allocations.

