### Allocation concealment

Each study site will receive a block of sequentially numbered, sealed, and opaque envelopes containing treatment allocation for either ‘SLT’ or ‘Drops’. Opaque envelopes will be opened in order of sequence per site. A unique study code will be assigned to each patient at randomisation, consisting of a three-digit randomisation number along with the patient’s initials.

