### Outcome measures

#### Health-related QoL (HRQOL)

Considering (a) the substantial side effects of topical medication(s) and poor adherence and (b) its considerable impact on daily living and QoL, HRQoL parameters are our critical outcomes to determine the treatment of choice for glaucoma. The *primary patient-centred outcome* will be assessed by significant changes in two glaucoma-specific scales and one generic HRQoL instrument at 6 weeks and at 6, 12, and 24 months post-treatment. These tools include the following:*Glaucoma Outcome Assessment Tool (GOAT):* We have developed a glaucoma-specific QoL item bank, GOAT, which contains 342 items across 10 specific QoL domains [36]. An item bank is a pool of calibrated items that measure a defined underlying trait such as QoL and becomes operational by the use of computer adaptive testing [37].*The Glau-QoL questionnaire:* The Glau-QoL is a comprehensive glaucoma-specific QoL instrument and has been validated in patients with glaucoma [38].*The AQoL-7D:* The AQoL-7D is a health-related multi-attribute utility instrument to assess QoL [39, 40]. This descriptive system comprises seven domains describing QoL (including vision) with levels of increasing severity. A scoring algorithm, based on general population values for health states defined by the descriptive system, is used to assign utilities to each health state (domain) described by the instrument and overall QoL. The AQoL-7D has been used in several RCTs in Australia and its overall and subscale measures have been found to be sensitive to interventions [41–44]. All QoL outcome measures will be interviewer-administered.

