#### Clinical efficacy

To assess clinical efficacy (IOP reduction success), Chi square tests will be used and multivariable logistic regression models with odds ratios (OR) and 95 % CI will be built. Other analyses will be tailored to the nature of the secondary outcome data. Numerical data (for example, IOP and visual acuity) and dichotomous data (presence/absence) will be analysed by the GEE. Survival data (for example, time-to-VF (visual field) progression, IOP becoming uncontrolled again) will be analysed using survival analysis. Stepwise multiple regression analyses for secondary outcomes will evaluate a similar set of potential explanatory factors (covariates) in addition to treatment assignment and those evaluated for the primary analysis. Time-varying covariates will be used for analyses evaluating repeated measures of the outcome, if appropriate. Standard errors of estimates from log-linear models will take account of possible over-dispersion with respect to the assumed models.

To determine the impact of SLT (single or multiple applications) on safety, surgical complications, and common side effects associated with glaucoma treatment, Chi square tests will be used initially and regression models with ORs and 95 % CI will be built. Where appropriate, Poisson regression will be used to compare event rates (for example, adverse events). To determine the predictors of IOP reduction success, survival curves will be constructed using the Kaplan-Meier method. Cox proportional hazards method will be used to adjust for confounders. Hazard ratios (HR) with 95 % CI will be provided to estimate the relative risk.

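### The primary QoL model's open-ended covariate list does not name the baseline QoL score, centre or glaucoma type, and the article describes the randomisation inconsistently

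*Protocol article*

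**What the plan says.** **Adjustment.** The Primary analysis section plans GEE or generalised linear mixed models for the repeated QoL scores. Covariates are to be chosen in advance for their association with QoL in the literature: "These include clinical variables (for example, baseline glaucoma severity, visual field, visual acuity, optic disc changes, duration of glaucoma", followed by age and gender as sociodemographic examples. Seven variables are named, none of them the baseline score of the scale under analysis, the clinical centre or the type of glaucoma. The Baseline characteristics section sends strongly imbalanced baseline variables to a sensitivity analysis only. Glaucoma type enters the analysis only under Planned subgroup analyses, and centre enters no analysis.

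**Baseline scores exist.** The primary outcome "will be assessed by significant changes in two glaucoma-specific scales and one generic HRQoL instrument". The Economic analysis section also relies on effectiveness, defined by AQoL-7D utilities, at baseline as well as follow-up.

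**Randomisation.** The Methods/Design section says that the study "is a multi-centred, cluster randomised, controlled, clinical trial". The Randomisation section says "Randomisation, per person, will be stratified by clinical centre and type of glaucoma" and "The randomization number will be assigned to a patient sequentially according to the order of enrolment within the stratum". The Allocation concealment section gives each site a block of numbered envelopes and adds: "Opaque envelopes will be opened in order of sequence per site".

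**The concern.** A patient's baseline score on the same scale is usually among the strongest predictors of the later score, so it is the first covariate one expects in the primary model. The stratification factors come next: if randomisation is balanced within strata and the strata are prognostic, an analysis that ignores them overstates the standard error. The article names seven other variables and a selection rule. That rule could admit the baseline score, but it gives no ground for including centre.

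The randomisation text raises a different problem. A reader cannot tell from it whether the unit is the patient or a cluster, or whether stratification by glaucoma type was put into practice. The first determines whether the sample size is valid. The second affects both the balance behind the planned POAG and XFG subgroup analyses and which factors the model should reflect.

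**Working it through.** **1. The plan's own sample size.** Inputs from Sample size estimation: difference 0.156 logit, effect size 0.3, so SD = 0.156/0.3 = 0.52; 80% power; 5% level, two-sided.

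n per group = 2 × (1.960 + 0.842)² / 0.3² = 174.4, rounded up to **175**, as stated. The t-test version gives 175.4, rounded up to 176, the figure given for the AQoL-7D. Neither contains a design effect or a covariate, so both describe individual randomisation.

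**2. Baseline score.** The documents give no baseline-to-24-month correlation r, so a range is assumed. Adjustment multiplies the residual variance by (1 − r²), so the effective effect size is 0.3/√(1 − r²). Patients left after the stated attrition: 193 × 0.85 = 164 per group. Power = Φ(effective d / √(2/164) − 1.960), with √(2/164) = 0.1104.

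| r (assumed) | effective d | power at 164 | n per group for 80% |
|---|---|---|---|
| 0 (unadjusted) | 0.300 | 77.5% (t-test 77.3%) | 175 |
| 0.3 | 0.314 | 81.3% | 159 |
| 0.5 | 0.346 | 88.0% | 131 |
| 0.7 | 0.420 | 96.7% | 89 |

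**3. Strata.** Suppose centre and type explain a fraction R² of the variance (assumed) and the arms are balanced within strata. An analysis that ignores them has true alpha = 2 × [1 − Φ(1.960/√(1 − R²))]. Power is shown at 175 per group.

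| R² (assumed) | true alpha, strata ignored | power, strata ignored | power, strata adjusted |
|---|---|---|---|
| 0.02 | 0.048 | 80.4% | 80.9% |
| 0.05 | 0.044 | 80.7% | 82.1% |
| 0.10 | 0.039 | 81.4% | 84.1% |

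**4. Unit of randomisation.** Methods/Design says cluster. Interventions randomises patients 1:1, Randomisation works per person, Allocation concealment gives each patient a code at randomisation, and step 1 shows no design effect. One label stands against four consistent descriptions.

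**5. Envelopes.** Randomisation assigns numbers in order within a centre-by-type stratum. Allocation concealment opens envelopes in order within a site and does not mention type. A single list per site would not stratify by type. Separate numbered sets per type at each site would satisfy both sections. The article does not say which was used.

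**6. Timing.** Trial status gives January 2013 to December 2016. If the end date is the last 24-month visit, enrolment ended by about December 2014, before publication in September 2015.

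**The case against.** The strongest reply is that nothing has been excluded. The covariates are given as examples, the statistical section refers to a pre-specified analytical plan that is not shown, and the selection rule could bring in the baseline score. That stands: the three variables are not named, and no more can be said.

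The power comparison is also open to challenge, because the plan is an adjusted longitudinal model and not a 24-month t-test. If baseline is a response with a common mean in both arms, most of the gain is already there. If the analysis amounts to change scores, the effective effect size is 0.3/√(2(1 − r)), and power at 164 per group is about 63%, 77.5% and 94% for r = 0.3, 0.5 and 0.7. The comparator is then lower at r = 0.3 and higher at r = 0.7. The article settles neither point, so the gain in step 2 is conditional.

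The strata argument also has a limit. If a site held only one envelope sequence, type was not balanced by design, and leaving it out causes no conservatism from that source.

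A reader might go further and infer that the covariates would remove part of the treatment effect, since optic disc change is also a secondary outcome and the article says "Time-varying covariates will be used for analyses evaluating repeated measures of the outcome, if appropriate". The documents do not support this for the primary model. The inclusion criteria use the same optic disc wording for a baseline finding, and the covariate list opens with baseline severity. The time-varying sentence is in the Clinical efficacy section, follows the regressions for secondary outcomes, and is conditional.

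**Conclusion.** The point holds as a matter of precision and clear wording, not of bias. The primary model should name the baseline score, centre and glaucoma type. Relative to an unadjusted 24-month comparison at 164 per group, the baseline score is worth about 4, 11 or 19 percentage points of power at assumed r of 0.3, 0.5 or 0.7. How much of this the planned model already captures cannot be told from the article. The effect of the strata is small: alpha between 0.048 and 0.039 for an assumed R² of 2-10%, and only if stratification worked.

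The word 'cluster' plainly contradicts the rest of the article. It is tempting to conclude that the sample size is therefore invalid, but every operational passage describes individual allocation, so a wording error is much the likelier explanation. It is likewise tempting to say that stratification by glaucoma type failed. The text shows an ambiguity between two sections, not a failure.

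**What to change.** - **Primary analysis:** name the baseline score of the same instrument, glaucoma type and centre (small centres pooled, or centre as a random effect) as covariates in the primary model, alongside those already listed. State that all covariates, including optic disc status, are baseline values.
- **Methods/Design:** delete 'cluster'.
- **Allocation concealment and Randomisation:** state whether each site held one envelope sequence or a separate one per glaucoma type, and describe what was actually done. As recruitment is probably complete, a new envelope series would be no remedy.

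The cost is a few sentences and one deleted word. No new data are needed: centre and type are recorded for randomisation, and baseline scores are implied by the change outcome. The model wording should be settled before any comparison by treatment is seen.

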### Specific aims

Aim 1: Our first aim is to compare the effect of SLT and topical medication on glaucoma-specific QoL at 6 weeks and at 6, 12, and 24 months post-treatment (primary outcome).

Aim 2: Our second aim is to quantify the cost-effectiveness of SLT treatment compared with glaucoma medication treatment.

Aim 3: Our third aim is to determine factors associated with treatment outcomes at 12 and 24 months post-SLT, including the rate of IOP success, defined as >25 % reduction in IOP from baseline measurements.

Aim 4: Our final aim is to assess the impact of SLT and eye drops on safety, laser-linked complications, and common side effects for glaucoma patients after the initiation of treatment.

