### Statistical analysis plan

All data analyses will be conducted according to a pre-specified analytical plan using Stata version 12.1.0 (Stata Corp, College Station, TX). All hypothesis testing will be performed at the 5 % two-sided significance level. Analyses and data summaries will be carried out using the intention to treat (ITT) population. The ITT population is defined as all patients registered for active follow-up regardless of non-adherence with the intervention. All patients will be analysed according to the intervention that they were randomised to. A per-protocol analysis will be considered if there are a considerable number of protocol violators.

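### The sample size is set at an unadjusted 5 % for each QoL instrument, but the primary analysis applies Bonferroni without stating the family or exempting GOAT

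*Protocol article*

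**What the plan says.** All places are in the protocol article.

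**Sizing.** Sample size estimation works from HRQoL at 24 months. For the two glaucoma-specific scales, where the target is d = 0.3 or 0.156 logit, it reads: "at 80 % power with a 5 % level of significance, 175 patients will be needed in each group". For the AQoL-7D, with the same effect size, it reads: "with 80 % power at 5 % level of significance; 176 patients will be needed for each group". It makes no allowance for multiplicity.

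**Test level.** The Statistical analysis plan section says: "All hypothesis testing will be performed at the 5 % two-sided significance level".

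**Multiplicity.** The Primary analysis section plans a separate longitudinal regression for each QoL parameter and adds: "To handle multiplicity in the multiple regression models, Bonferroni adjustment will be used". It gives neither the family nor the divisor, and exempts no test.

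**Primary outcome.** The wording differs between sections:
- Specific aims, Aim 1: "glaucoma-specific QoL at 6 weeks and at 6, 12, and 24 months post-treatment (primary outcome".
- Health-related QoL (HRQOL): "significant changes in two glaucoma-specific scales and one generic HRQoL instrument at 6 weeks and at 6, 12, and 24 months".
- Primary analysis: "The GOAT will be our main primary outcome".
- Sample size estimation: HRQoL at 24 months, sized on all three instruments.
- Discussion: HRQoL as assessed by three patient-reported measures.

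**The concern.** The power claim and the testing rule use different significance levels. If the Bonferroni sentence reaches the primary comparison, the level used for sizing is not the level at which the result will be judged, and 80 % overstates the power for each instrument.

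The success criterion is also open. Suppose the 24-month GOAT comparison gives p = 0.03. Under the 5 % rule in the Statistical analysis plan and Sample size estimation sections it is positive. Under Bonferroni over three instruments the threshold is 0.05/3 = 0.0167 and it is negative. The article does not say which rule decides, so the choice could be made, or be suspected of having been made, after the data are seen.

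**Working it through.** **Inputs.** From Sample size estimation: d = 0.3 on every instrument (0.156 logit, so SD = 0.156/0.3 = 0.52, for GOAT and Glau-QoL); 80 % power; 5 % level; 193 enrolled per group; 15 % attrition. Two-sided testing is from the Statistical analysis plan section. The Bonferroni divisor and the correlation between instruments are assumptions, because the article gives neither.

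**1. Reproduce the stated size.** n per group = 2(z₁₋α/₂ + z₀.₈₀)²/d².
- At α = 0.05: 2(1.960 + 0.842)²/0.09 = 174.4, so 175. The noncentral t gives 176.
- Both stated figures reproduce at an unadjusted 5 %. With α = 0.05/3 the same formula gives 232.6, so 233 (235 by noncentral t).

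**2. Power for one given instrument.** Power ≈ Φ(d√(n/2) − z₁₋α/₂). The noncentrality d√(n/2) is 2.806 at n = 175, 2.814 at 176 and 2.717 at 164. The 164 is 193 × 0.85.

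| Assumed family | α per test | z | n = 175 | n = 176 | n = 164 |
|---|---|---|---|---|---|
| GOAT at 24 months alone | 0.05 | 1.960 | 80.1 % | 80.4 % | 77.5 % |
| 3 instruments | 0.0167 | 2.394 | 66.0 % | 66.3 % | 62.7 % |
| 3 instruments × 4 visits | 0.0042 | 2.865 | 47.7 % | 48.0 % | 44.1 % |

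The noncentral t gives values 0.2 to 0.7 percentage points lower (for example 65.6 %, 65.9 % and 62.2 % in the second row).

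The 164 column includes a second, separate problem: 193 enrolled with 15 % attrition leaves fewer than 175. The drop due to Bonferroni alone is the one seen at 175-176, from 80 % to 66 %.

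**3. Power for at least one significant instrument.** If the three instruments are alternatives, any one of which would carry the claim, the relevant quantity is the probability that at least one passes at 0.0167. I took d = 0.3 on all three, trivariate normal test statistics and a common correlation r.

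| Assumed r | n = 175-176 | n = 164 |
|---|---|---|
| 0.5 | 87-88 % | 85 % |
| 0.7 | 83 % | 80 % |
| 0.8 | 80 % | 77 % |
| 0.9 | 76 % | 73 % |

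**4. Limit of the check.** These are simple two-group comparisons, as in the article's own sizing. The planned covariate-adjusted longitudinal model may have more power; the article gives no inputs from which to compute the gain.

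**The case against.** The strongest reply is that the article already has a lead test. GOAT is called the main primary outcome, sizing is at 24 months, and all tests are at two-sided 5 %. Read together, these make GOAT at 24 months the deciding comparison, with 80 % power at 175 per group and no loss. Bonferroni would then apply only across the other regressions. This reading is plausible, but the text does not secure it. Calling one outcome the main primary implies that there are others. The GOAT sentence names no visit, GOAT is described as covering 10 domains without one score being named, and the Bonferroni sentence stands under the primary analysis with no exemption.

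A second reply is that the divisor belongs in a separate analysis plan, which the article mentions and which is not shown. For the divisor and the choice of GOAT score alone, that is fair. It does not cover a conflict between two statements that the article itself makes: a power claim at 5 % and an adjusted primary analysis.

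A third reply is that Bonferroni is a valid method. That stands. Preferring fixed-order testing is a matter of taste.

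A reader might also infer that the primary outcome is settled as three instruments at four visits, so that the trial's power has collapsed to 62-66 % or below. The documents do not support this. The 62-66 % range assumes a divisor of three, not twelve; it is power for one given instrument; and its low end comes partly from the attrition shortfall. Twelve separate tests are not planned in those terms, since each parameter gets one longitudinal model.

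**Conclusion.** The point holds as a mismatch between sizing level and testing rule, together with inconsistent wording of the primary outcome. It does not establish that the trial is underpowered.

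The size depends on what is meant:
- **GOAT alone at 24 months, 5 %:** about 80 % at 175 per group, 77 % at 164. No multiplicity loss.
- **Three instruments under Bonferroni, each needing its own claim:** about 66 % per instrument at 175-176, against the stated 80 %.
- **Three instruments under Bonferroni, any one sufficient:** about 76 to 88 % at 175-176 for assumed correlations of 0.9 to 0.5, so the loss is nil to modest.

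All figures rest on d = 0.3 and a simple two-group comparison. The second and third also rest on a divisor of three that the article does not state. The ambiguity about which rule decides the trial rests on no assumption and needs correcting in any case.

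**What to change.** In Specific aims, Health-related QoL (HRQOL) and Primary analysis, name the between-arm difference in one pre-specified GOAT score at 24 months as the sole primary test at two-sided 5 %. Make Glau-QoL, AQoL-7D, the earlier visits and the domain scores secondary, and limit the Bonferroni sentence to those secondary tests. Fixed-order testing of the secondary instruments would be an acceptable alternative. Bring the Discussion's description of the primary outcome into line.

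This changes wording only and keeps the basis of the planned sample size. The cost is that Glau-QoL and AQoL-7D are no longer primary.

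If all three instruments are to stay primary under Bonferroni, state the divisor. With a divisor of three, restate per-instrument power in Sample size estimation as about 66 % at 175-176 evaluable per group; keeping 80 % would need about 233 to 235 evaluable per group.
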